Despite not adhering exactly to the recommended model of CIT, these studies observed positive results such as an improvement in motor function, mobility, dynamic balance, discharge weight symmetry, gait ability, gait speed, length and width of step, and force of foot ground contact [26, 28]. However, in view of the above information, the investigation of the effects of the original LE-CIT protocol on gait functionality and balance of chronic hemiparetic patients following a stroke was not completely clarified.

The following research question was established to examine the effects of LE-CIT *vs* intensive conventional therapy on gait functionality and balance, as well as the transference of these gains in therapy to the environment outside the clinical setting in chronic hemiparetic patients following a stroke: is LE-CIT more effective compared with intensive conventional therapy with regard to gait functionality and balance in people suffering from stroke?

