### Sample size and justification

After a sample size calculation, realized through a pilot study with 10 randomized patients in each group, using G*Power3.1.9.2 Software, we employed a matched-pair t-test *a priori*, using mean and standard deviation of Mini-BESTest (with an effect size of 0.93—sample size of 12 for each group) and 6minWT (with an effect size of 0.65—sample size of 21 for each group) as the primary outcome. Considering for analysis an α 0.05 and β 0.80, 21 patients were estimated for each group, totalizing 42 patients for this study.

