#### Balance measure

*Mini-Balance Evaluation Systems Test (Mini-BESTest)*: This is a tool used to evaluate balance control. It comprises 14 items divided into 4 subscales (anticipatory postural control, reactive postural control, sensory orientation, and gait stability). Each item is classified in an ordinal scale of 3 points (0 = severe and 2 = normal) and the maximum score is 28 points [43–45]. Tsang et al. [46] concluded that the MDC for this tool for post stroke patients is 3 points.

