#### Data analyses

The software Excel (Microsoft) will be used to tabulate the data and the software SPSS will be used to do the statistical analysis. A significance level of 5% will be adopted.

We will use the Kolmogorov-Smirnov test to analyze the normality of the data. For the characterization of the sample and baseline comparison to test the homogeneity of the sample, the Qui-Quadrado will be used, but if we find statistical differences between the groups we will also analyze the clinical relevance of these differences.

The results will be compared in relation to the type of intervention and at the three timepoints proposed in this study (pre-treatment, post-treatment, and at 6 month follow-up) using the two-way analyses of variance, ANOVA, and the Bonferroni post-hoc test or Friedman, depending on the parameterization of the data.

To analyze the direction and magnitude of outcomes, we will use the Pearson or Spearman test of correlation.

The results will be described with mean and standard deviation for each group and mean and standard deviation of differences between groups and confidence interval.

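### The non-parametric alternative, the Friedman test, has no arm term, so an outcome sent down that branch has no named test of LE-CIT against control

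*Protocol article*

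**What the plan says.** The research question at the end of the Background is a contrast between arms: "is LE-CIT more effective compared with intensive conventional therapy with regard to gait functionality and balance in people suffering from stroke".

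The Data analyses section sets up two factors, group and time: "The results will be compared in relation to the type of intervention and at the three timepoints proposed in this study". The method is a two-way "ANOVA, and the Bonferroni post-hoc test or Friedman, depending on the parameterization of the data". Just before this it says: "We will use the Kolmogorov-Smirnov test to analyze the normality of the data". The level is fixed by "A significance level of 5% will be adopted".

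The other tests named in that section serve other purposes: chi-square for baseline characteristics, and Pearson or Spearman for correlation. The section closes by saying that results will be described by group means and SDs, and by the mean and SD of the group differences with a confidence interval. It gives neither a method nor a level for that interval.

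Of the two primary outcomes, the Mini-BESTest is a sum of 14 items with a maximum of 28. On the items, the Balance measure section says: "Each item is classified in an ordinal scale of 3 points". The other, the 6-min walk test, is a distance.

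**The concern.** The question has two factors (arm and time), and the alternative test has one (time). Friedman cannot stand in for a two-way analysis. Pooled over all 42 patients, it ignores allocation. Run separately in each arm, it gives two statements about time and none about the difference between arms.

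For a primary outcome that takes this branch, the article names no test that answers its own question. An analyst left with only within-arm p-values may be drawn to read significance in LE-CIT and non-significance in control as evidence for LE-CIT. That reading does not hold the type I error at the stated level. The control arm receives intensive therapy at 2.5 h/day over the same 15 days, so real improvement in both arms is a reasonable case to consider.

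**Working it through.** **1. The plan's own figure.** The sample size section gives "6minWT (with an effect size of 0.65—sample size of 21 for each group) as the primary outcome" and "Considering for analysis an α 0.05 and β 0.80, 21 patients were estimated for each group, totalizing 42 patients for this study". Reading the 0.80 as power, a two-sided paired t-test at 5% with noncentrality d√n gives:
- d = 0.65, n = 21: power 0.809, the smallest n reaching 0.80.
- d = 0.93, n = 12: power 0.834, the smallest n reaching 0.80.

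Both stated sizes are reproduced. The value 0.65 is used below only as a convenient scale. Treating it as a within-arm standardised change is my assumption, because the article does not say what the pairs are.

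**2. What Friedman can see.** With n patients, k time points and rank sums R_j:

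Q = 12 / [n k (k+1)] × ΣR_j² − 3n(k+1)

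For n = 42 and k = 3 this is ΣR_j²/42 − 504. Only ranks within a patient enter, and arm labels appear nowhere. A numerical check on one simulated data set gave Q = 0.1905, p = 0.909. The result was identical after adding 100 to every value in one arm, and after shuffling the order of the patients.

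**3. Pooled Friedman against a between-arm rank test.** Assumptions, not from the article: normal data, SD 1, within-patient correlation 0.7, 21 per arm, the change at T1 fully kept at T2, 3,000 simulated trials per scenario. The comparator is a Mann-Whitney test on the T0-to-T1 change.

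| True situation | Pooled Friedman rejects | Mann-Whitney on change rejects |
|---|---|---|
| Both arms improve by 0.65 SD (no arm difference) | 99.8% | 5.2% |
| Only LE-CIT improves, by 0.65 SD | 60% | about 74% |
| Arms move by +0.325 and −0.325 SD (arm difference 0.65) | 4.0% | 73% |

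Friedman rejects almost always when there is no arm difference, and at about the nominal rate when there is one but the average change is zero.

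**4. If Friedman were run by arm and the p-values compared.** Suppose both arms improve equally, and let p be the chance that one arm is significant. The arms are independent, so:
- P(exactly one arm significant) = 2p(1−p)
- P(LE-CIT alone significant) = p(1−p)

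The second expression cannot exceed 0.25, reached at p = 0.5. It exceeds 0.025 whenever p lies between (1 − √0.9)/2 = 0.026 and (1 + √0.9)/2 = 0.974.

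Simulated within-arm Friedman, 21 per arm, three time points, normal data:

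| Assumed within-arm change (mean / SD of change) | Exactly one arm significant | LE-CIT alone |
|---|---|---|
| 0.50, T2 gain fully, half or not kept | 47-51% | 24-25% |
| 0.65, T2 gain fully, half or not kept | 40-47% | 20-24% |
| 0.84, T2 gain fully kept | about 16-17% | 8-9% |

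The last row is the 0.65 SD improvement of step 3 on this scale: 0.65/√(2 × (1 − 0.7)) = 0.65/0.775 = 0.84. Each arm is then significant about 90-91% of the time, and 0.91 × 0.09 = 0.08.

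A two-time-point paired t-test gives 0.809 × 0.191 = 0.15 at 0.65 and 0.587 × 0.413 = 0.24 at 0.50. That is a different test, shown only for comparison.

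**The case against.** **A reader might infer that the trial has no test of LE-CIT against control.** The article does not support that. Its leading method, the two-way ANOVA, contains the group factor and addresses the research question. Only an outcome sent to the alternative is affected.

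**The promised interval for the group difference could serve as a test.** If it is a 95% between-group interval, whether it excludes zero corresponds to a 5% test, and nothing confines it to the ANOVA branch. This stands in part: an estimate of the arm difference would still be reported. But it is offered as description, it rests on means in the branch chosen because means were thought unsuitable, and its method and level are not given.

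**A reader might infer that the plan will compare two within-arm p-values.** Nothing in the article says so. The error rates in step 4 describe what would happen under that practice. They are not the plan's error rate.

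**The trigger is only implied.** The article never states that a Kolmogorov-Smirnov rejection leads to Friedman, and it gives no threshold. That is the natural reading, but not a stated rule. How often the branch would be taken is also uncertain. For rounded 0-28 scores with assumed means of 14-22 and SDs of 5-6, one sample of 21 is rejected about 7-12% of the time with the Lilliefors correction and almost never without it. The rate rises if several samples are tested. For the 6-min walk test the article gives no particular reason to expect the branch.

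**An article condenses a fuller plan.** That excuses omissions. Here a specific test is named for a purpose it cannot serve.

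**Conclusion.** The point holds as a conditional defect. The named alternative to the two-way ANOVA contains neither group nor group-by-time, so for any outcome that takes that branch no named test addresses the research question. This follows from the form of the Friedman statistic and needs no assumption about the data. The branch is plausible for the Mini-BESTest, and its probability cannot be fixed from the article.

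The size of the harm depends on what would be done in place of an arm comparison. If within-arm results were set against each other, and both arms truly improved by the same 0.50 to 0.84 standardised change, false claims for LE-CIT would run at roughly 8-25% against a nominal 2.5%. Those figures assume normal data and 21 per arm. They fall as the common change becomes so large that both arms are nearly always significant. The main ANOVA branch is untouched, but the rule should be corrected before outcomes are analysed.

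**What to change.** Replace Friedman as the between-group fallback with a method that contains the arm factor and is applied at both T1 and T2, since the article plans comparison at all three time points. Any of these would do, chosen in advance:
- a baseline-adjusted comparison of arms with a permutation p-value for the arm effect;
- a rank-based ANCOVA;
- a between-group rank test on change from T0.

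State that the arms are compared for every outcome whatever a normality test shows. If Friedman is kept, label it a within-arm description that supports no claim about LE-CIT against control. State the method and level of the interval for the group difference.

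The ANOVA branch need not be replaced to close this gap. The cost is one sentence of analysis text and a little code; design, sample size and data collection do not change.

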**Methods:**

The study adopts a randomized, controlled, single-blinded study design. Forty-two patients, who suffered a stroke, who were in the chronic phase of recovery (>6 months), with gait disability (no community gait), and who were able to walk at least 10 m with or without the advice or support of 1 person, will be randomly allocated to 2 groups: the LE-CIT group or the control group (intensive conventional therapy). People will be excluded if they have speech deficits that render them unable to understand and/or answer properly to evaluation scales and exercises selected for the protocol and/or if they have suffered any clinical event between the screening and the beginning of the protocol. Outcome will be assessed at baseline (T0), immediately after the intervention (T1), and after 6 months (T2). The outcome measures chosen for this trial are as follows: 6-min walk test (6minWT), 10-m walk test (10mWT), timed up and go (TUG), 3-D gait analysis (3DGA), Mini Balance Evaluation Systems Test (Mini-BESTest), and as a secondary measure, Lower Extremity Motor Activity Log will be evaluated (LE-MAL). The participants in both groups will receive 15 consecutive days of daily exercise. The participants in the LE-CIT group will be submitted to this protocol 2.5 h/day for 15 consecutive days. It will include (1) intensive supervised training, (2) use of shaping as strategy for motor training, and (3) application of a transfer package (plus 30 min). The control group will receive conventional physiotherapy for 2.5 h/day over 15 consecutive days (the same period as the CIT intervention). Repeated measures analyses will be made to compare differences and define clinically relevant changes between groups.

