### Randomization, blinding, and treatment allocation

#### Randomization procedure

Randomization will be realized through the allocation of vacancies (21 for each group) by a researcher who has no contact with the evaluation or intervention process. We created a spreadsheet with this sequence of allocation (intervention or control) and the distribution of the participants into the groups was made by sorting the order according to inclusion criteria and recruitment.

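### Correlation cannot measure the size of the treatment effect, and an SD of between-group differences is undefined for independent arms: name the mean difference with its SE and 95% CI as the effect measure

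*Protocol article*

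**What the plan says.** In the protocol article, Data analyses, the arms are compared over the three time points "using the two-way analyses of variance, ANOVA, and the Bonferroni post-hoc test or Friedman, depending on the parameterization of the data". A separate sentence then says: "To analyze the direction and magnitude of outcomes, we will use the Pearson or Spearman test of correlation". It does not say which variables are correlated. The following sentence promises "mean and standard deviation for each group and mean and standard deviation of differences between groups and confidence interval". The section sets the significance level ("A significance level of 5% will be adopted") but does not give the level of the interval.

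The arms are independent. In the abstract, patients "will be randomly allocated to 2 groups: the LE-CIT group or the control group (intensive conventional therapy"). The randomization section says: "Randomization will be realized through the allocation of vacancies (21 for each group"). No patient-level matching is described. Pairing appears only under Sample size and justification: "we employed a matched-pair t-test".

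Two reference values are cited for the primary outcomes: a clinically important difference of 28 to 42 m for the 6minWT (Walking performance measures) and a minimal detectable change of 3 points for the Mini-BESTest (Balance measure). The abstract also says the analysis should identify clinically relevant changes between groups.

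**The concern.** The sentence gives correlation a job it cannot do. Judging a 6minWT result against 28 to 42 m needs a between-group difference in metres with a valid interval. A correlation coefficient has no units, and in its usual forms (visit with visit, test with test) it does not respond to a uniform gain or loss. If it were reported as the magnitude of effect, a beneficial, null or harmful shift could give the same number.

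The next sentence names the right quantity, a mean difference, but attaches a wrong measure of spread. A standard deviation of differences exists when each observation in one arm has a partner in the other. Here it does not. An analyst following the text literally would have to invent a pairing or report a different quantity under that name, and readers or meta-analysts could take the figure for something else.

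**Working it through.** **Plan's own figures.** The sentences at issue state none. The nearest are the 12 and 21 per group in the sample-size section. They come back exactly from a paired t-test at two-sided 0.05 (sidedness assumed) and 80% power: effect size 0.93 with n = 12 gives power 0.834, and 0.65 with n = 21 gives 0.809. So a paired formula was used there. That says nothing about how the outcomes will be analysed.

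**1. Correlation and a constant shift.** Corr(X, Y + c) = Cov(X, Y + c) / [SD(X) · SD(Y + c)] = Corr(X, Y), because a constant changes neither the covariance nor the SD. Ranks do not change either, so Spearman behaves the same way. Numerical check with assumed values: pre-treatment mean 200 m and SD 60 m; post = 0.8 × pre + 40 + noise (SD 36 m) + shift. The post SD is √(0.64 × 3600 + 1296) = 60 m, so r = 0.8 × 60/60 = 0.80. Simulated results:

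| Shift (m) | Pearson | Spearman |
|---|---|---|
| 0 | 0.800 | 0.785 |
| 28 | 0.801 | 0.787 |
| 42 | 0.799 | 0.784 |
| 100 | 0.802 | 0.786 |

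**2. The one form that tracks treatment.** A correlation of outcome with group membership does move with the effect: r = d/√(d² + 4) for equal arms. The text does not describe this, and the result is still not in metres. Take 35 m, the midpoint of 28 to 42, with assumed SDs:
- SD 60 m: d = 0.583, r = 0.28
- SD 100 m: d = 0.35, r = 0.17
- SD 140 m: d = 0.25, r = 0.12

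The same gain in metres gives three different magnitudes.

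**3. SD of differences between groups.** For any chosen pairing, SD² = s_A² + s_B² − 2·r_AB·s_A·s_B, where r_AB is the correlation created by that pairing. With unpaired arms r_AB is arbitrary. In one simulated data set of 21 + 21 (SD 40 m assumed), the two extreme pairings gave SDs of 18 and 90 m. The mean difference (44 m), pooled SD (46 m) and standard error (46 × √(2/21) = 14 m) do not depend on pairing.

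**4. What the promised mean difference and CI deliver.** With 21 per arm, SE = √(1/21 + 1/21) = 0.309 SD. The 95% half-width is 2.021 (t, 40 df) × 0.309 = 0.624 SD. An observed 0.65 SD would have an interval of 0.03 to 1.27, and 0.93 SD would have 0.31 to 1.55. At the assumed SDs of 60, 100 and 140 m the half-width is 0.624 × SD = 37, 62 and 87 m.

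**5. Adjusting for T0.** If the T0–T1 correlation is 0.80 (assumed), the residual SD is √(1 − 0.64) = 0.60 of the outcome SD. The half-width falls to about 0.60 × 0.624 = 0.37 SD, ignoring the degree of freedom spent and any chance imbalance at T0. At an SD of 60 m that is about 22 m instead of 37 m. A lower correlation gives a smaller gain.

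**The case against.** The strongest objection is that the plan already contains the right effect measure. The mean difference between groups and a confidence interval are promised in the sentence after the correlation sentence, and both are well defined without pairing. This stands. A reader might infer that the stated measures cannot show the size of the treatment effect at all, but the text does not support that. Only the SD is undefined.

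A reader might also infer from the matched-pair t-test that the arms will be compared by a paired analysis. No section plans this. The paired test appears only in the sample-size calculation, and the analysis is two-way ANOVA or Friedman on independently allocated arms. P-values under arbitrary pairings would describe an analysis nobody has proposed.

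The correlation sentence speaks of outcomes, not of the treatment effect. Sign and strength of association between, say, the Mini-BESTest and the 6minWT is a plausible reading, and an article may leave the variable list to the full plan. This is fair, and it is why keeping the correlations as exploratory is acceptable. It does not rescue the wording, which states a purpose (direction and magnitude) without tying it to associations, in a section about comparing treatments.

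Finally, a T0-adjusted estimate adds a model to the planned ANOVA. That is true and is counted as a cost below.

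**Conclusion.** The point holds in a limited form. Correlation is misassigned as the measure of direction and magnitude: its invariance to a constant shift is algebraic and needs no assumption. The SD of between-group differences has no unique value for independent arms. It should be the standard error of the mean difference, or else the SD of within-patient change in each arm. The plan can still show effect size through the promised mean difference and interval, so this is a defect in how the effect is defined and reported, not a failure of the trial to estimate it.

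The invariance and the 0.624 SD half-width follow from the design and 21 completers per arm. The figures in metres, the 0.80 pre-post correlation and the 18 to 90 m range rest on assumed SDs or one simulated data set, and are illustrations only.

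**What to change.** Delete the correlation sentence, or keep it as an exploratory analysis of associations between named outcomes. Replace the effect statement with wording such as:

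For each outcome we report mean and SD per arm and visit, and the T0-adjusted LE-CIT minus control difference at T1 and, where measured, at T2, in original units, with its standard error and 95% CI for independent arms. The 6minWT difference is read against the cited clinically important difference of 28 to 42 m. The 3-point Mini-BESTest value is cited as a minimal detectable change only.

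The qualifier on T2 is needed because Table 1 schedules 3-D gait analysis at T0 and T1 only. The last sentence matters because a minimal detectable change marks measurement error, not clinical importance.

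The cost is a few sentences and one extra model that uses T0 data already collected. The small downside is that the effect estimate comes from a baseline-adjusted model reported alongside the planned two-way ANOVA. The two need not agree exactly, so the text should say that the adjusted difference is the effect estimate.

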## Results

For the execution of this trial, a period of 4 years has been predicted from the first patient recruitment to the last evaluation (6 month follow-up) of the last patient (Table 2). The participation of patients in this trial will last 7 months: initial evaluation, intervention, and 6 months after the end of protocol. The first study results are expected to be published by the end of 2021.

## Discussion

This paper describes the methodology of the first randomized controlled single-blinded clinical trial analyzing the effects of LE-CIT on the gait and balance of hemiparetic stroke survivors. Although studies on CIT for UE have been published over recent decades and a substantial body of evidence has been produced [11–15], LE-CIT has had little investigation. A few studies have been published, but these do not contain all the components proposed by the creator of the protocol. Recently, a description of LE-CIT was published which includes 4 pillars: (1) intensive supervised training delivered for 3.5h/day for 10 consecutive weekdays, (2) use of shaping as a strategy for motor training, (3) application of a transfer package, and (4) strongly encouraging the use of the more affected LE with improved coordination [47]. The same group has published the first study applying this version of the LE-CIT protocol to one patient with chronic hemiparesis, as a case report. In their study, the patient was submitted to LE-CIT for 10 consecutive days and by the end of the protocol an improvement was observed in LE-MAL(which infers the quality and confidence in using of the weaker LE) and balance score (measured by the Berg Balance Scale), as well as small changes in endurance and walking speed [49].

Our clinical trial proposal has high clinical significance for neurological rehabilitation, particularly for the stroke population. It is known that physical rehabilitation can be more effective than usual care or no attention in improving motor function, balance, and gait velocity [50]. Additionally, bigger doses of physical therapy provide significant benefits for motor function [50] and an average improvement of approximately 10% for both walking ability and activities of daily living [51].

Indeed, we believe that more important than motor advances is how far the patient can transfer these gains outside of the clinical setting, as improvements in clinical outcomes often do not translate to changes in community walking [52, 53]. It is believed that there is no “learned non-use phenomenon” related to lower extremities, instead “learned misuse” is attributed to these patients. Is that true? How can we explain that, even as their health improves, these patients continue not to walk as much as they are capable of doing? Ardestani (2019) suggests that perhaps the changes induced by the training in rehabilitation programs is just maintained in follow-up measures if there is greater paretic limb use to achieve increased daily stepping [54]. That is the reason why LE-CIT includes intensive supervised training linked with the transfer package; in this way, it can ensure that the motor gains will be incorporated into daily life activities [16, 47].

van Vliet et al. [55] also discuss the need for empowering stroke survivors in their own recovery since the health services will never have the capacity to ensure maximum motor function. This is a big challenge during the rehabilitation period and has been considered in the LE-CIT protocol by guaranteeing that the patient will be sufficiently engaged in using their more affected limb in daily activities. This will be achieved through the homework list (as part of the transference package). Alternatively, if the patient still finds a reason for not using the affected limb, they will then discuss this with the therapist in an attempt to find a solution to encourage the use of this limb in an efficient and confident way [16, 47].

Evidence from upper extremities supports the idea that patients who were subjected to CIT had better arm motor function [56] and greater use of the affected arm in daily life when compared with a control group, straight after the protocol and on follow-up assessments [57] (Table 2). This improvement provides additional evidence that CIT patients who receive the transfer package show significantly greater increases in gray matter in the hippocampus and sensory and motor areas when compared with a group that has not received it [57].

